#### Baseline visit (Day 0)

After completion of baseline data collection, participants who meet the inclusion criteria and do not meet any exclusion criteria will be enrolled in the trial. Participants will be randomly assigned, in a 1:1 ratio, to either empagliflozin or continue with the original treatment plan. Subjects will complete all baseline examinations, including CPET, ultrasound cardiogram, New York Heart Association functional class and MLHFQ scores. Following baseline data collection, participants assigned to the empagliflozin group will receive empagliflozin 10 mg once daily in addition to their original treatment, while those in the control group will continue with their original treatment regimen.

#### Follow-up visit (Day 84 ± 3)

We will conduct repeat assessments of all examinations including CPET and echocardiography to evaluate efficacy and safety.

### Data collection and analysis

#### Sample collection and laboratory measurements

Blood samples will be collected during the screening visit and follow-up visits by professional nurses in The Third Affiliated Hospital of Guangzhou Medical University and measure blood routine examination, biochemical indices, NT-proBNP in clinical lab. Women of reproductive age will be asked to provide urine samples for a pregnancy test during the screening visit.

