**Exclusion criteria**
(1) Diabetes;
(2) Acute coronary syndrome whihin the last 2 months or planned coronary revascularization during the trial;
(3) Atrial fibrillation, cardiovascular and cerebrovascular events related to atrial fibrillation in the last 3 months;
(4) Hepatic dysfunction, defined by serum levels of transaminases more than three times the upper limit of normal at screening;
(5) Using SGLT2i within 4 weeks prior to randomization;
(6) Diseases that affect the results of CPET include arthropathy, peripheral vascular disease, lung disease and other diseases;
(7) The subject's resting ECG has the following abnormalities: (a) ventricular pre-excitation syndrome; (b) ventricular pacing rhythm; (c) resting ST segment depression of more than 2 mm; (d) left bundle branch block or any intraventricular conduction delay with QRS duration greater than 120 ms；
(8) Congenital heart defects, progressive decompensated congestive heart failure, severe valvular disease, hypertrophic obstructive cardiomyopathy, severe uncontrolled hypertension (sitting systolic blood pressure >180mmHg or diastolic blood pressure >110mmHg), severe anemia, suspected or known arterial dissection, acute myocarditis or pericardial effusion, active endocarditis, thrombophlebitis, or pulmonary embolism.
(9) History of bleeding tendency, cerebral hemorrhage, or epilepsy requiring anticonvulsant medication.
(10) Pregnant woman or breastfeeding woman.
(11) Participated in any other trials or use of any investigational drugs within the 30 days prior to enrollment.
(12) Drug abuse. The patient has a history of alcohol abuse or known drug dependence in the past 2 years.

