### Study timelines

#### Screening visit (Day −14 ± 3)

The timeline and inspection items are listed in Table 3. At the screening visit, participants will receive ECG, eligibility laboratory tests, vital signs measurement, and drug history registration. Laboratory data will include urine pregnancy testing, complete blood count, biochemical indexes, NT-proBNP.

**Table 3 Tab3:** Schedule of assessments

Timelines	Screening Visit	Baseline Visit	Follow-Up Visit
Week	−2	0	12
Day	−14±3	0	84±3
Informed consent	✓	X	X
Inclusion/exclusion criteria	✓	✓	X
Concomitant medication	✓	✓	✓
Vital signs	✓	✓	✓
Physical examination	✓	✓	✓
urine pregnancy testing^a^	✓	X	X
12-lead ECG	✓	X	✓
CPET	X	✓	✓
Cardiac ultrasound	X	✓	✓
Laboratory tests^b^	X	✓	✓
New York Heart Association functional class	X	✓	✓
Minnesota Heart Failure Quality of Life Scale	X	✓	✓
Medical history	✓	✓	X
Adverse events^c^	✓	✓	✓

^a^Urine pregnancy testing for women of reproductive age

^b^Laboratory tests include: complete blood count, eGFR, ALT, AST, NT-proBNP

^c^Adverse events include: urinary system, hypoglycemia, renal function damage, etc

✓ indicates that the item must be completed at that time

X indicates that the item is not required at that time

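### The only scheduled pregnancy test is 11 to 17 days old at first dose because Table 3 does not require one at Day 0; separately, Table 3 omits the screening laboratory tests that the text orders

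*Protocol article*

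**What the plan says.** **Pregnancy test.** Under Sample collection and laboratory measurements, the article states: "Women of reproductive age will be asked to provide urine samples for a pregnancy test during the screening visit". The text under Screening visit (Day −14 ± 3) also lists the test there. Table 3 ticks it at screening and enters X at the baseline and week 12 visits; its key explains that "X indicates that the item is not required at that time".

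**Eligibility and dosing.** Exclusion criterion 10 in Table 1 reads "Pregnant woman or breastfeeding woman". Table 3 ticks the inclusion/exclusion row at both screening and Day 0. Under Baseline visit (Day 0), once baseline data are complete, "participants who meet the inclusion criteria and do not meet any exclusion criteria will be enrolled in the trial". The same section has patients randomized at that visit, with empagliflozin started after baseline data collection.

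**Laboratory tests.** The screening-visit text says: "At the screening visit, participants will receive ECG, eligibility laboratory tests, vital signs measurement, and drug history registration". It continues: "Laboratory data will include urine pregnancy testing, complete blood count, biochemical indexes, NT-proBNP". The blood-sample sentence under Sample collection and laboratory measurements names the screening and follow-up visits, and does not name Day 0. Exclusion criterion 4 sets hepatic dysfunction as "defined by serum levels of transaminases more than three times the upper limit of normal at screening". The laboratory row of Table 3, however, has X at screening and ticks at Day 0 and week 12. Its footnote reads: "Laboratory tests include: complete blood count, eGFR, ALT, AST, NT-proBNP".

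**The concern.** The Day 0 visit is the last point at which a pregnant woman can be kept out of the trial before she is randomized and possibly dosed. The protocol re-checks the exclusion criteria there but does not require the one test that bears directly on criterion 10. The re-check therefore rests on a screening result or on what the patient reports. A pregnancy too early to show at screening could pass unnoticed to first dose.

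The laboratory matter is one of consistency. A site that works from Table 3 alone would draw no blood at screening, although criterion 4 asks for transaminases at that visit. A site that works from the blood-sample sentence alone would find no Day 0 draw listed, although Table 3 requires one. ALT, AST, eGFR and NT-proBNP are secondary endpoints expressed as change from baseline, so the article should be uniform about when these samples are taken.

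**Working it through.** **Age of the pregnancy result at first dose**

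Inputs: the screening window is Day −14 ± 3 (section heading and Table 3). First dose is taken as Day 0; this is read from Baseline visit (Day 0) and is not given as a dosing date.

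- Earliest screening day: −14 − 3 = −17.
- Latest screening day: −14 + 3 = −11.
- Age of result = 0 − screening day, which gives 0 − (−11) = 11 days to 0 − (−17) = 17 days.
- With a test at Day 0 before randomization, the age is 0 days.

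If the first tablet is taken after Day 0, the gap is longer than 11 to 17 days.

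**Number of extra tests**

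The article does not say how many women of reproductive age are expected. Assuming 0% to 10% of the 86 patients: 0 × 86 = 0 to 0.10 × 86 = 8.6, so 0 to 9 dipsticks.

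**Laboratory tests, place by place**

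| Place in the article | Screening | Day 0 | Week 12 / follow-up |
|---|---|---|---|
| Table 3, laboratory row | not required | required | required |
| Screening-visit text | required, for eligibility | – | – |
| Blood-sample sentence | drawn | not named | drawn |
| Exclusion criterion 4 | transaminases needed | – | – |

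A dash means that the place is silent. In the screening column, Table 3 stands alone against three other places. In the Day 0 column, Table 3 requires a draw and the blood-sample sentence omits it. The first is a contradiction; the second is only an omission.

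**Who can still benefit**

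Trial status says that enrolment is continuing and expects recruitment to end by the close of 2025. Publication is dated 7 April 2026. From 31 December 2025 to 7 April 2026 is 31 + 28 + 31 + 7 = 97 days. A patient randomized on 31 December 2025 would have the week 12 visit at Day 84 ± 3, that is 81 to 87 days later, or 97 − 87 = 10 to 97 − 81 = 16 days before publication. If recruitment ran to plan, no patient is left to whom a Day 0 test could apply.

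**The case against.** The best case for the plan is that the pregnancy schedule is consistent. The screening text, Table 3 and the sample-collection section all give one test at screening, and nothing in the document demands a second. X means not required, so an investigator may still test. Medical history and physical examination are ticked at Day 0, physicians review history before the exercise test, and pregnancy is a withdrawal criterion if it is discovered later. All of this is true and lowers the risk. But history-taking is not a pregnancy test, and withdrawal acts only after exposure. The point survives as a cheap improvement to a stated entry.

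A reader might go further and infer that a Day 0 dipstick would probably catch a pregnancy missed at screening. The documents give no figure for this, so only the age of the result can be stated.

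On laboratory tests, a reader might infer that criterion 4 cannot be checked at screening. That requires reading Table 3 apart from the text in the same section, which orders eligibility laboratory tests at that visit. The X is more likely a slip, or the row may list only the outcome panel. A reader might also infer that change in the four laboratory endpoints runs from the screening sample and so covers a longer interval. The blood-sample sentence does not say so; it merely leaves Day 0 out, while Table 3 has a column for the Baseline Visit with laboratory tests ticked.

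**Conclusion.** Both points hold, and both are minor.

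The required pregnancy result is 11 to 17 days old at first dose, where a Day 0 test would make it 0 days. This assumes dosing on Day 0. The number of women concerned is unknown; 0 to 9 follows only from the assumed 0% to 10% range. The schedule does not contradict itself here. It is a choice that can be bettered at very small cost, for patients not yet randomized.

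The screening entry for laboratory tests in Table 3 does contradict the screening-visit text, the blood-sample sentence and criterion 4. The consequence is unclear instructions and nothing more. The reasonable reading is that eligibility bloods are drawn at screening and baseline bloods at Day 0. Any departure from this would apply to both arms alike, so no bias is claimed. The primary endpoint, the sample size and the primary analysis are unaffected.

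**What to change.** 1. In Table 3, change the Day 0 entry for the urine pregnancy test from X to required, before randomization, for women of reproductive age. The cost is one table cell and a few dipsticks (0 to 9 under the stated assumption) at a visit already attended.
2. In Table 3, tick laboratory tests at screening for eligibility. Keep the Day 0 tick and state that Day 0 is the baseline for change in ALT, AST, eGFR and NT-proBNP.
3. Add Day 0 to the blood-sample sentence under Sample collection and laboratory measurements.

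Items 2 and 3 are editorial and ask for no test that some part of the article does not already plan. If enrolment has closed, item 1 comes too late. The trial report should then state at which visits the laboratory samples were taken and which one served as baseline.

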#### Cardiopulmonary exercise testing

CPET will be conducted by professional physicians in the cardiac function department. Prior to the test, physicians will thoroughly review the patient’s medical history and medication history exclude any contraindications and obtain signed informed consent for the trial. CPET consists of two parts, static pulmonary function testing and the ramp protocol. Static pulmonary function testing will obtain respiratory parameters such as forced vital capacity and maximal flow-volume loops. The ramp protocol includes several stages: a rest period, an unloaded warm-up period, a power load period, and a recovery period. The power increment for the ramp protocol is calculated using the following formula: Predicted unloaded VO_2_ (ml·min^−1^) = 150 + [6 × weight (kg)]; Predicted peak VO_2_ (ml·min^−1^) = [height (cm) - age (years)] × 20 (males) or × 14 (females) [11]. Finally, parameters such as peak VO_2_, AT, and VE/VCO_2_ are obtained. CPET reports will be issued by professional physicians and reviewed by senior physicians.

#### Cardiac ultrasound

Echocardiography is performed by professional physicians. It primarily measures indices reflecting left ventricular systolic and diastolic function, including LVEF, LVEDV, LAV, E/E', and PAP. The modified Simpson’s method is utilized for LVEF measurement, tissue Doppler imaging is employed to measure E and e′ values to derive E/e′, and PAP is assessed. Three-dimensional color Doppler echocardiography is used for LAV measurement.

### Adverse events and safety

Adverse events are categorized into two aspects: CPET-related adverse events and empagliflozin-related adverse events. Empagliflozin-related most common adverse reactions include hypoglycemia, hypotension, deterioration of kidney function, urinary tract infection, elevated LDL cholesterol levels will be monitored. According to the results from Phase III clinical trials, empagliflozin is generally well tolerated, with a low incidence of adverse events (2.2% in empagliflozin 10 mg) [12]. Additionally, common adverse reactions are generally of mild intensity, rarely led to drug discontinuation, and tended not to recur. All adverse events will be documented in the case report form for evaluation and reporting to the Clinical Research and Applied Ethics Committee of The Third Affiliated Hospital of Guangzhou Medical University.

### Data management and monitoring

After each follow-up visit, research data will be collected and documented in the case report form. All data will be kept by the investigators. Upon completion of the study, the data will be entered into the Clinical Trial Management Public Platform (medresman.org.cn) for data sharing. All data will be preserved permanently.

No interim analysis is planned for this trial due to the short study duration, moderate sample size, and the well-established safety profile of empagliflozin. All efficacy and safety outcomes will be analyzed and reported collectively upon completion of data collection.

### Data protected

All electronic participant data will be stored permanently on a hospital-standard encrypted server. Access is strictly limited to authorized research personnel directly involved in the study. All study staff receive mandatory training on data confidentiality covering relevant regulations and institutional policies. Physical documents containing participant identifiers are kept in locked cabinets within access-controlled rooms.

### Compliance evaluation

The study period is 3 months, during which subjects are required to attend monthly clinic follow-ups. Compliance will be measured using a combination of methods to enhance reliability: (1) the number of completed follow-up visits, (2) pill count based on returned medication bottles, and (3) verification of medication usage during each clinic visit. In addition, regular telephone follow-ups will be conducted to reinforce adherence and remind subjects to take their medication as scheduled.

### Strategies to enhance adherence

To improve participants’ adherence, we will (1) have our professional physicians conduct regular follow-ups, (2) provide all examinations free of charge during the trial, and (3) offer a modest compensation upon completion. These details have been added to the revised manuscript.

### Statistical consideration

#### Sample size assumptions

This study adopted a one-to-one parallel design, evaluating the sample size based on the change in peak oxygen uptake before and after treatment as the primary efficacy endpoint. It was designed as a superiority trial to compare the means of two groups. Based on previous studies, the increase in peak oxygen uptake after 6 months of treatment was estimated to be 1.1 ± 2.6 ml/kg/min for the empagliflozin group and −0.5 ± 1.9 ml/kg/min for the control group [13]. It was assumed that a difference greater than 0 between the test and control groups would be clinically significant. The combined standard deviation of the change values for both groups was set at 2.4 ml/kg/min. The sample size was calculated using the following formula:$$N_c=\frac{\left(Z_{1-\alpha}+Z_{1-\beta}\right)^2\;\sigma^2\;\left(1+{\displaystyle\frac1r}\right)}{\left(\mu_E-\mu_c-\triangle\right)^2}$$where *N*: required sample size per group; Z_1−α/2_: critical *Z*-value for the two-sided significance level (α); *Z*_1−β_: critical *Z*-value for the desired statistical power (1-β); *σ* pooled standard deviation of the change in peak VO₂; μ_E_: mean change in peak VO₂ for the empagliflozin group; μ_C_: mean change in peak VO₂ for the control group; Δ: the non-inferiority or superiority margin. Here, Δ = 0 defines the test for superiority; *r*: allocation ratio (n_E_/n_C_).

In this study, *α* = 0.0 25, *β* = 0.2, Z_1−α_ = 1.96, *Z*_1−β_ = 0.8416, μ E - μ C = 1.6, *σ* = 2.4, *r* = 1, Δ = 0. Calculations show that 36 subjects are required in each group. Consequently, a total of 86 subjects (43 individuals in each group) are included, accounting for an approximate dropout rate of 20%.

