**Methods and analysis:**

This study is a single-center, open-label, randomized controlled trial. We will randomly (1:1) assign 86 patients with an ejection fraction of more than 40% and class II–III heart failure to receive empagliflozin (10 mg once daily) or to maintain their original treatment regimen. The treatment duration will be 12 weeks. The primary endpoint is the evaluation of changes in peak oxygen uptake (peak VO2) after a 12-week period using cardiopulmonary exercise testing (CPET). The secondary endpoints encompassed additional parameters of CPET and echocardiography, N-terminal pro-B-type natriuretic peptide level, alanine aminotransferase level, aspartate transaminase level, estimated glomerular filtration rate level, New York Heart Association functional classification, and scores from the Minnesota Living with Heart Failure Questionnaire. Safety events associated with empagliflozin and CPET will be monitored.

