### Statistical analysis

Statistical analysis will be conducted using SAS 9.4. All statistical tests will be two-tailed, and a *p*-value of less than 0.05 will be considered statistically significant, unless otherwise specified.

For continuous data, statistical descriptions will include counts, means, standard deviations, medians, minimum and maximum values, and upper and lower quartiles. For categorical data, counts and percentages will be used for statistical descriptions. Between-group comparisons of continuous data will be conducted using *t*-tests or rank-sum tests, while categorical data will be compared using chi-square tests or Fisher’s exact test. Non-parametric methods, such as the Wilcoxon rank-sum test, will be employed for ordinal data. Continuous data will be presented as mean ± standard deviation (x ± s). Normality tests will be conducted first, and if both groups meet the assumptions of normality and have equal variances, a *t*-test will be used for between-group comparisons. Otherwise, we will consider the non-parametric Wilcoxon rank-sum test.

Missing data for the primary efficacy endpoint will be addressed using multiple imputation under the assumption of missing at random. Twenty imputed datasets will be generated using predictive mean matching incorporating baseline characteristics. The pooled estimates from the imputed datasets will be used for the primary analysis. Additionally, a complete-case analysis will be conducted as a validation to evaluate the robustness of the results.

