#### Primary efficacy endpoint analysis

The primary efficacy endpoint, the change in peak VO₂ from baseline to week 12, will be analyzed using an analysis of covariance model. Additionally, we will compute the one-sided 97.5% confidence interval for the difference in changes in peak oxygen uptake before and after treatment, comparing both the test and control groups. If the lower boundary of this one-sided 97.5% confidence interval exceed 0, we will conclude that the test group demonstrates superiority over the control group. Furthermore, exploratory multivariate models will be applied to adjust for other potential baseline confounders.

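### The 20% dropout allowance does not fit the sample size: 43 per arm leaves about 34 evaluable, not the required 36, so power at that dropout falls slightly below 80%

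*Protocol article*

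**What the plan says.** The section Sample size assumptions gives every input to the calculation: one-sided α = 0.025 (Z = 1.96), β = 0.2 (Z = 0.8416), a difference in mean change of 1.6 ml/kg/min, equal allocation and a margin of zero. On the standard deviation it says "The combined standard deviation of the change values for both groups was set at 2.4 ml/kg/min". The result is stated as "Calculations show that 36 subjects are required in each group".

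The enrolment target follows directly: "Consequently, a total of 86 subjects (43 individuals in each group) are included, accounting for an approximate dropout rate of 20" per cent. No formula is shown for the step from 36 to 43. The abstract repeats the total, saying that the trial will "assign 86 patients with an ejection fraction of more than 40" per cent.

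Two statements elsewhere bear on what happens to patients who drop out. Primary efficacy endpoint analysis specifies an analysis of covariance and declares superiority "If the lower boundary of this one-sided 97.5% confidence interval exceed 0". For missing primary data, Statistical analysis says "Twenty imputed datasets will be generated using predictive mean matching incorporating baseline characteristics", with a complete-case analysis as a check.

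**The concern.** A dropout rate is the fraction of enrolled patients who are lost. To finish with n evaluable patients, one enrols n / (1 − dropout). Multiplying by (1 + dropout) gives too few, and the gap widens as the rate rises. At 20% the two rules differ by two patients per arm here, and the article's 43 matches the multiplication.

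The printed design figures therefore do not agree with one another. If the trial loses the 20% it says it has allowed for, it ends below the 36 per arm that it says it needs. Readers will also judge the achieved attrition against the printed 20%. A trial that lost 18 to 20% could report staying within its planned allowance while having fallen short of its own requirement.

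**Working it through.** **Inputs** (all from Sample size assumptions): Z for α = 1.96, Z for β = 0.8416, difference = 1.6, SD = 2.4, r = 1, Δ = 0, dropout about 20%, 43 enrolled per arm.

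**1. Reproduce the plan's figure before dropout.**

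n = (1.96 + 0.8416)² × 2.4² × (1 + 1/1) / (1.6 − 0)² = 35.32, rounded up to **36 per arm**. This agrees with the article. One-sided 0.025 and two-sided 0.05 give the same result, since both use Z = 1.96.

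**2. Inflate for dropout.**

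| Rule | Per arm | Total |
|---|---|---|
| 36 / (1 − 0.20) | 45 | 90 |
| 36 × 1.20 | 43.2, giving 43 | 86 |
| Article | 43 | 86 |

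Starting from the unrounded 35.32 does not help: 35.32 / 0.80 = 44.15, still above 43.

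**3. What 43 per arm delivers.**

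- Evaluable at 20% loss: 43 × 0.80 = 34.4 per arm (68.8 in total), against 36 required.
- Loss that can be absorbed while keeping 36: 1 − 36/43 = 7/43 = 16.3%.
- The same against the unrounded requirement: 1 − 35.32/43 = 17.9%.

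**4. Power at the retained numbers.**

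The normal approximation that matches the article's formula is power = Φ( 1.6 / (2.4 × √(2/n)) − 1.96 ). For n = 34 this is Φ(2.749 − 1.96) = Φ(0.789) = 78.5%. The t-test column uses the noncentral t distribution with 2n − 2 degrees of freedom.

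| Evaluable per arm | Normal formula | t-test |
|---|---|---|
| 34 | 78.5% | 77.3% |
| 34.4 | 79.0% | 77.8% |
| 35 | 79.6% | 78.5% |
| 36 | 80.7% | 79.7% |

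Since 45 × 0.80 = 36, enrolling 45 per arm would restore the 36-per-arm row.

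**The case against.** The arithmetic is hard to dispute. The case on the other side concerns its size and its certainty.

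- **The loss is very small.** By the article's own formula, power at 20% dropout is 78.5 to 79.0%, which is 1.0 to 1.5 points under target. The t-test figure of 77.3% includes a gap that has nothing to do with dropout, because a t-test at the full 36 per arm already gives only 79.7%. Like for like, the t-test loss is 79.7% to 77.8% at 34.4 per arm. This stands, and the point should not be read as a seriously underpowered trial.
- **The 20% is called approximate.** That softens the mismatch without closing it. The supported allowance is about 16%, or 17.9% on the most generous reading.
- **The factor of 1.2 is inferred.** This is true, since no inflation formula is printed. The inconsistency does not depend on it: 43 × 0.80 is below 36 however 43 was reached.
- **Covariance adjustment may recover the loss.** If the covariate is baseline peak VO2 (the section does not name it) and its correlation with the change is ρ, the required number scales by (1 − ρ²). Setting 35.32 × (1 − ρ²) = 34.4 gives ρ of about 0.16. At 34.4 per arm, ρ = 0.1 gives 79.4% and ρ = 0.3 gives 82.6% by the normal formula. These values of ρ are assumptions. The article gives no correlation and its sizing takes no credit for one. The offset is plausible in practice but does not make the printed statement correct.
- **The SD is slightly conservative.** The quoted arm SDs of 2.6 and 1.9 pool to √((2.6² + 1.9²)/2) = 2.28, with which 34 per arm would give about 81 to 83% power. The article nevertheless fixes 2.4, so this bears on the practical consequence and not on the stated calculation.
- **Missing values will be imputed.** Imputation from baseline characteristics recovers little when the week-12 value itself is absent. The Schedule of assessments (Table 3) has no exercise test between baseline and week 12 from which to borrow. The complete-case check would run on about 34 per arm in any event.

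**Conclusion.** The concern holds. Under the sizing assumptions as printed (unadjusted comparison, difference 1.6, SD 2.4, one-sided 0.025), a total of 86, a dropout of 20% and a power of 80% are mutually inconsistent. The total is 4 patients short of the 90 that the stated dropout implies, and the allowance actually provided is about 16%. The loss of power at 20% dropout is small: 1 to 1.5 points below 80% by the article's formula, and 2 to 3 points below 80% by a t-test, part of which is the difference between the two methods. Adjustment for baseline or a smaller SD could make good the difference, but neither was counted in the calculation. This is a minor arithmetic error in a stated design figure. It does not affect the endpoint, the analysis or the decision rule.

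**What to change.** Keep 86 patients and correct the sentence, for example: *Enrolling 86 patients (43 per arm) allows for about 16% dropout at 80% power; at 20% dropout about 34 per arm are evaluable and power is about 77 to 78%.* If a single method is preferred, quote 78.5% (normal formula) or 77.3% (t-test) at 34 per arm and name the method.

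If the sponsor wishes to keep both 20% and 80%, the matching total is 90 (45 per arm), and the abstract must change with it. That option may be of limited use now, since Trial status expected recruitment to finish by the end of 2025.

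The restatement costs one sentence and a slightly less favourable figure. It needs no extra patients and no change to the design or analysis.
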